#### Allocation

Following informed consent and baseline measures, participants will be randomized 1:1 to the experimental or control condition. The randomization will be conducted by one of the members of the research team using a web-based randomization program for medical research (https://webcrf.medisin.ntnu.no). Participants will be informed immediately about what condition they are assigned to. Blinding of participants or researchers will not be practically feasible.

#### Assessment

Baseline data (-*t*_1_) will be collected prior to randomization and consists of the FIS skills test, administered by members of the research team, as well as several self-report measures of secondary outcomes and potential correlates of the FIS. See above for details about measures and outcomes. Session-by-session self-reported stress- and self-efficacy measures as well as reflective log entries will be completed by students in the intervention group at each clinic and immediately before and after each treatment session they attend (*t*1 –*t*_10_). Following the 10-week apprenticeship period (*t*_11_), students in both conditions will complete the FIS-test at the university, using different stimulus clips from those that were used pre-intervention, as well as self-report measures of secondary outcomes. At this point in time, students in the intervention group as well as therapists will be invited to focus group interviews. Follow-up data (*t*_12_) will be collected from students in both conditions two years after the completion of the apprenticeship condition, and consist of the FIS test as well as self-reported secondary outcomes.

#### Data management

Participants will be given a numeric study ID which is identifiable by a coding list only accessible to the principal investigator. Data will be manually double-entered by research assistants who are blind to allocation.

### Sample size

Sample size was determined based on parameters on the main outcome measure FIS from three samples [42, 43, 71]. A sample size of 100 yields an 80% probability for detecting a medium intervention effect (*d* = 0.5) with a one-sided alpha level of .05. Allowing for 20% attrition, we aim to include 120 student participants.

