### Participants and eligibility criteria

Student participants will be first-year students at the clinical psychology program (*N* = 120), randomized 1:1 to training-as-usual or training-as-usual plus apprenticeship. All first-year students are eligible to participate in this study (no exclusion criteria). The apprenticeship intervention will be performed by therapist employees (licensed clinical psychologists, psychiatrists, psychiatric nurses, or from other professions) of the three participating clinics. All therapist employed outpatient teams in these clinics are eligible to participate.

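### Enrolling 120 students does not allow for 20% attrition: it leaves 96, not the 100 on which the stated 80% power rests

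*Protocol article*

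**What the plan says.** The Sample size section of the protocol article makes two linked statements. The first sets the number needed for analysis: "A sample size of 100 yields an 80% probability for detecting a medium intervention effect", for a standardised difference of d = 0.5 and "with a one-sided alpha level of .05". The second sets the recruitment target: "Allowing for 20% attrition, we aim to include 120 student participants".

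The Abstract and the Participants and eligibility criteria section repeat the total of 120. The latter also gives the allocation: "randomized 1:1 to training-as-usual or training-as-usual plus apprenticeship". Nowhere does the article define attrition differently or name another target for the number analysed.

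**The concern.** Attrition is a fraction of those enrolled. An allowance for it should therefore satisfy enrolled × (1 − attrition) = number needed. With 120 enrolled and 20% lost, the left side is 96, while the plan needs 100. The required number, the loss rate and the enrolment target cannot all be right together.

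Two things are at stake. The power claimed for the trial does not hold at the attrition it says it allows for, at least for the unadjusted comparison that the stated inputs describe. The allowance is also the yardstick against which retention will later be judged: with a loss between 16.7% and 20%, the trial could report attrition within its allowance and still have fewer than 100 students.

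**Working it through.** **Inputs**, all from the Sample size section except the allocation ratio (Participants and eligibility criteria):

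- number needed: 100, i.e. 50 per arm at 1:1
- effect: d = 0.5
- test: one-sided, alpha = .05
- power: 80%
- attrition: 20%
- enrolment: 120

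**Step 1: reproduce the 100.** By the normal approximation, n per arm = 2(z₀.₉₅ + z₀.₈₀)²/d² = 2(1.645 + 0.842)²/0.25 ≈ 49.5, rounded up to 50, so 100 in total. At 50 per arm the power is 80.4% by the normal approximation and 79.9% by the noncentral t. The 100 is confirmed. Only the one-sided test yields it; a two-sided test at .05 would need 63 per arm by the normal approximation.

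**Step 2: reproduce the 120.**

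| Rule | Calculation | Enrol |
|---|---|---|
| Divide by the retained fraction | 100 / (1 − 0.20) | 125 (126 for equal arms) |
| Add the percentage to the base | 100 × (1 + 0.20) | 120 |

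The stated 120 matches the second rule, which does not retain 100 after a 20% loss. The gap is 5 students (5/120 = 4.2%).

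**Step 3: what 120 delivers.**

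- Completers after 20% loss: 120 × 0.80 = 96, i.e. 48 per arm.
- Largest loss that keeps 100: 1 − 100/120 = 16.7%.

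**Step 4: effect on power.** For the unadjusted two-sample comparison, the noncentrality parameter is d√(N/4), with N − 2 degrees of freedom:

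| Completers | Noncentrality | Power (noncentral t) |
|---|---|---|
| 96 | 0.5 × √24 = 2.449 | 78.4% |
| 100 | 0.5 × √25 = 2.500 | 79.9% |
| 102 | 0.5 × √25.5 = 2.525 | 80.6% |

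The loss from 100 to 96 is about 1.5 percentage points. By the normal approximation, power at 96 is 78.9%. The row for 102 shows that 100 has no slack to absorb the shortfall: 51 per arm is the first size to reach 80% by the t-test. The difference between 79.9% and 80% is rounding and is not a separate error.

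**Step 5: power under the planned analysis.** The Statistics and data analyses section plans regression adjusted for the pre-intervention score. The article gives no pre-post correlation r for the primary outcome, so the values below are assumptions. With 96 completers, the adjusted effect is 0.5/√(1 − r²), on 93 degrees of freedom:

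| Assumed r | Power |
|---|---|
| 0.1 | 78.8% |
| 0.2 | 79.9% |
| 0.21 | 80.0% |
| 0.3 | 81.7% |
| 0.5 | 87.8% |

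**The case against.** The strongest reply is that nothing of substance changes. The shortfall is 4 students and about 1.5 points of nominal power, in a trial that describes itself as exploratory. The unadjusted test is also not the planned analysis: a pre-post correlation of about 0.21 would restore 80% power with 96 completers. Multiple imputation is planned as well (printed as implementation), and students lost after randomization will have baseline scores, so completers need not be the whole analysed set. Finally, the article shows no formula; 120 could be a rounded or feasible target.

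Much of this stands. The consequence is small, and this is not evidence of a materially underpowered trial. The conflict with 80% power holds for the unadjusted calculation and may disappear under adjustment. How 120 was reached is inferred from the match with 100 × 1.20.

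The reply does not repair the sentence. The plan does not invoke baseline adjustment or a correlation to support its 80%. Imputing missing outcomes from baseline and condition adds little information, and the plan itself treats 100 as the number to be protected from attrition. However 120 was chosen, it does not cover a 20% loss from a target of 100.

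The section also does not say whether the 20% refers to the post-intervention or the two-year assessment, so no conclusion about follow-up losses is drawn here.

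**Conclusion.** The point holds. The attrition allowance is wrong as written: 120 enrolled covers a loss of 16.7%, and a 20% loss leaves 96 students, 4 below the stated 100. Enrolment matching the stated allowance would be 125, or 126 for equal arms. Unadjusted one-sided power at d = 0.5 is then 78.4%, not 80%.

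This rests on the plan's own inputs, on attrition meaning a fraction of those enrolled, and on equal loss in the two arms. The arithmetic is certain and the practical consequence is minor. Baseline adjustment probably offsets the lost power, but by an amount the article gives no means to calculate.

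**What to change.** Keep the target at 120 and correct the sentence in the Sample size section, in one of two ways:

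- state that enrolling 120 allows for 16.7% attrition while retaining 100; or
- state that 20% attrition would leave 96 completers, with about 78% power (one-sided .05, unadjusted).

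In either case, add the power for the planned baseline-adjusted model, with the assumed pre-post correlation and its source, and say which assessment the attrition figure refers to.

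The cost is one corrected sentence, a short addition and a slightly less favourable figure. No extra participants are needed. The article says that protocol modifications will be reported in later publications, so the correction can be made there.

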### Statistics and data analyses

Quantitative outcomes will be analyzed using regression models in which post-intervention and follow-up scores will be predicted by condition, controlled for pre-intervention scores and other possible covariates. Longitudinal models will examine the development over time on the session-by-session stress and self-efficacy measures. Missing data will be handled with multiple implementation. Qualitative data will be thematically analyzed.

### Data monitoring

There are no anticipated harmful consequences of participation in this study and therefore, no stopping guidelines are developed and no interim analyses are planned.

### Ethics approval and consent to participate

The study will be conducted in accordance with the Declaration of Helsinki. It was approved by the Regional Ethics Committee in Mid-Norway (REK) as an extension of a larger research project (2012/1498). Participation is voluntary and written, informed consent is obtained. No patient data will be collected in the project; in interviews and written log entries, students and therapists will be instructed not to share any identifiable client information. Students in the intervention group will sign a confidentiality agreement prior to the apprenticeship intervention. Therapists will obtain verbal consent to have a student co-therapist present in sessions from those of their patients that they consider to be suitable. The therapists will be responsible for the treatment delivered.

### Status and timeline

This publication is based on protocol version 1 (05-04-2021). Recruitment for the trial began on 09-20-2021, and is expected to be completed by October 2023.

## Discussion

This randomized controlled trial and qualitative investigation will explore the potential impact of applying an educational method widely practiced in other fields, the apprenticeship, to the training of future psychotherapists. We consider it to be a promising supplementary element to the traditional (e.g., coursework, clinical practice under supervision) as well as the newer (e.g., deliberate practice) methods of psychotherapist training. In their apprenticeships, students will be exposed to the complexity—and sometimes messiness and confusion—of psychotherapy as it is practiced in actual clinical settings. A variety of ways to respond to challenging interactions in therapy will be demonstrated by relatable role models. Importantly, students will have the opportunity to discuss and gain insight into what considerations lie behind these role models’ actions with their clients, as well as to try out their own therapeutic skills under close guidance. We expect this to be facilitative of students’ interpersonal skills, to increase their self-efficacy, decrease their performance anxiety and stress, and to advance their understanding of the practical psychological work. This would demonstrate a proof-of-concept by this study. We also expect it to be engaging and helpful for the experienced therapists to welcome student co-therapists into their therapy room.

### Strengths and limitations

The study has several important strengths. The experimental intervention is apprenticeship in a very simple form. The randomized controlled design will allow us to examine any additive effects of apprenticeship as a single element to training-as-usual while decreasing the influence of systematic biases on results. The qualitative data from several sources will help provide a more nuanced understanding of both students’ and therapists’ apprenticeship experiences. Interviews and reflective logs will supplement the quantitative measures, allow for unexpected findings to emerge, and be vital in generating hypotheses for future studies. We consider a sample of first-year psychology students to be ideal in testing the impact of apprenticeship on interpersonal skills; they are untainted by previous training and may have fewer preconceptions and be less preoccupied with the technical aspects of the specific treatment models than more advanced students perhaps would. Possibly, this demonstration and practical experience in real-world psychotherapy at the very beginning of their careers will provide them with a strong starting point from which to absorb and assimilate all subsequent learning experiences more effectively. The main outcome measure, the FIS performance test, assesses skills in standardized situations in which client variability is controlled for, and has been demonstrated to be highly predictive of client outcomes [72]. It is designed to tap therapist behaviors that are likely to be of importance regardless of what specific treatment model therapists adhere to and as such, we expect results to be generalizable to therapists of all theoretical orientations.

The main limitation of apprenticeship as a training method is perhaps the unpredictability of clinical work. In this study, there will be no control over what clients the students meet or what happens in sessions with those clients. Students’ exposure to challenging interpersonal interactions will be completely at random. It is also very possible that the therapists’ demonstration of interpersonal skills will be less than optimal. Arguably however, examples of what not to do can also be very educational. Moreover, observing therapists performing less than optimally can be a healthy antidote for students who may have perfectionistic tendencies. It is our hope that this early exposure to the complexity of psychotherapy, in conjunction with other educational methods, will help prepare them to the unpredictability that characterizes real-life clinical work [73].

Some of the design choices we have made inevitably result in certain limitations. The rotation of students between different therapists is intended to counteract therapist effects and ensure that students are exposed to a variety of different clients, therapists, and ways of conducting therapy. Disadvantages of therapist rotation is that students will be less able to form a secure relationship to one role model or to follow the full course of treatment with one client. Moreover, the apprenticeship intervention is shorter in duration and less intensive than the full-time apprenticeships that are perhaps more commonly practiced in other fields. The rationale behind this is both feasibility–the intervention needs to fit into the ongoing study program as well as the day-to-day practice at busy treatment clinics–and the acknowledgement of the importance of the other educational methods that this intervention is meant to supplement, but not replace.

### Implications

The aim of this study is to gain preliminary knowledge on a relatively simple and, hopefully, feasible training method intended to improve the treatment of mental health problems through the improved education of future therapists. Given the high prevalence and costs of mental health problems for individuals and society at large, we find the endeavor to educate more efficient psychotherapists of utmost importance.

### Dissemination plans

Upon completion, results will be published in peer-reviewed journals and presented at research conferences and other relevant arenas for research dissemination. Authorship to all future publications will be granted in accordance with the Vancouver recommendations. Any modifications to this protocol will be reported in subsequent publications.
